### Sample size

This randomized non-inferiority trial is designed to assess the non-inferiority of the defined ACH model compared to traditional inpatient hospital care. Based on preliminary analyses, we expect that the event proportion of the composite endpoint in the traditional brick-and-mortar hospital care arm will be approximately 30%. Additionally, we expect that the event rate in the ACH arm under the alternative hypothesis will be 30%. Sample size is based on the one-sided score test statistic for the non-inferiority test for an odds ratio of proportions. Given a non-inferiority odds ratio of 1.909, one-sided alpha of 0.025, and an interim analysis (defined under Interim Analysis), a sample size of 360 (180 per arm) is required to achieve 80% power. A non-inferiority margin expressed as an odds ratio of 1.909 with a 30% event rate in the traditional inpatient care arm is equivalent to a relative risk ratio of 1.5, a 45% event rate in the ACH arm, as the non-inferiority margin. EAST (Cytel) software was used for all sample size calculations.

### Statistical analysis

Logistic regression will be performed to assess the primary outcome. Analysis will be performed on all eligible patients who provide consent, are randomized, and start the intervention, following the intention-to-treat (ITT) principle. Cox proportional hazards regression analysis will also be performed to assess time-to-event; cumulative incidence curves will be plotted. If there is cross-over between treatment arms, a “per-protocol” analysis will be performed. In this per-protocol analysis, the ACH group would consider all patients who are randomized to ACH, with the follow-up censored at the time of crossing over to the control group; similarly, the control group would consider all patients who are randomized to control, with the follow-up censored at the time of crossing over to ACH. When analyzing continuous outcomes (i.e., cost and days alive out of hospital), a generalized linear model will be used, assuming a γ distribution with a log link, given the skewed nature of the data. When examining the long-term time-to-event outcomes beyond 30 days, a Cox proportional hazards model will be used when it may be necessary to account for censored data.

Because the baseline and outcome data will be obtained from the EHR, no significant missing data is expected. The study coordinators will check with patients during the end-of-study phone call regarding outcome events in case patients receive care outside of the study sites (Additional file 8). However, such events are anticipated to be rare in this patient population. In a previous trial of a HaH program, only 2 out of 91 patients received care outside the study sites [3].

Exploratory analyses such as machine learning approaches using causal tree will be performed to examine the heterogeneous treatment effect (HTE), i.e., which patients might benefit most from the intervention. Exploratory analyses will be performed stratified by acute and restorative phases.

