**Methods:**

We aim to enroll 360 acutely ill adult patients (≥18 years) who are admitted to three hospitals in Arizona, Florida, and Wisconsin, two of which are academic medical centers and one is a community-based practice. The eligibility criteria will follow what is used in routine practice determined by local clinical teams, including clinical stability, social stability, health insurance plans, and zip codes. Patients will be randomized 1:1 to ACH or traditional inpatient care, stratified by site. The primary outcome is a composite outcome of all-cause mortality and 30-day readmission. Secondary outcomes include individual outcomes in the composite endpoint, fall with injury, medication errors, emergency room visit, transfer to intensive care unit (ICU), cost, the number of days alive out of hospital, and patient-reported quality of life. A mixed-methods study will be conducted with patients, clinicians, and other staff to investigate their experience.

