### Randomization

Patients will be randomized in a 1:1 ratio to either ACH or traditional brick-and-mortar hospital care. The randomization algorithm will be generated within the Remote Data Capture (REDCap) software system, using stratified block randomization with blocks of random size. As the clinical trial will be stratified by site, randomization is then performed separately within each stratum level, utilizing blocks of random size. The study coordinators will implement the randomization in REDCap and assign participants. Due to the nature of the intervention, blinding is not feasible for trial participants and care providers. Of the study team members, the study coordinators, analysts, and the data manager will know the randomization due to their roles and responsibilities, including implementing randomization, ensuring data quality, and providing reports to the Data and Safety Monitoring Board (DSMB). The rest of the study team, e.g., the principal investigators and co-investigators, will be blinded to the allocation.

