### Baseline measurements

Patient-level baseline data will be collected from the Mayo Clinic electronic health record (EHR), including age, sex, race, ethnicity, address, and the primary diagnosis for admission. These data will be ascertained at the time of randomization.

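### Randomization is stratified by site but the stated primary analysis names no site term; if run unadjusted, its interval is slightly too wide, and the remedy must keep the odds ratio on the marginal scale of the 1.909 margin

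*Protocol article*

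**What the plan says.** - Protocol article, Randomization: "As the clinical trial will be stratified by site, randomization is then performed separately within each stratum level, utilizing blocks of random size". The Setting section describes the sites as two academic centres and one community hospital.
- Statistical analysis: "Logistic regression will be performed to assess the primary outcome". No covariates are listed, and site is neither included nor excluded.
- Sample size: "Sample size is based on the one-sided score test statistic for the non-inferiority test for an odds ratio of proportions". The margin is an odds ratio of 1.909, tied to overall rates of 30% (hospital) and 45% (ACH). Both arms are expected to have 30% events, and 180 per arm is said to give 80% power.
- Interim analysis: the stopping rule is written as the odds ratio comparing the two arms' event proportions, under the same plan as the primary endpoint.
- Baseline measurements: the variables collected are described as "including age, sex, race, ethnicity, address, and the primary diagnosis for admission".
- Statistical analysis plan: a fuller plan is to be finalized before database close. It is not shown.

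**The concern.** Blocking within site balances the arms within each hospital. If hospitals differ in death and readmission rates, that balance removes part of the sampling variation in the treatment comparison. A logistic model with arm alone does not credit this, so its standard error exceeds the estimator's true variability.

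At stake is a little precision in a trial with no power to spare. There is also a question of scale. The margin was built from overall rates, so the odds ratio compared with it should be marginal. A logistic model with site added reports a site-conditional odds ratio, which is a different quantity.

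**Working it through.** **Reproducing the plan's figure.** Inputs from Sample size: 30% in both arms, margin 1.909, one-sided alpha 0.025, power 80%.

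- Margin: (0.45/0.55)/(0.30/0.70) = 1.909; ln(1.909) = 0.6466.
- n per arm = (1.96 + 0.8416)² × [2/(0.30 × 0.70)] / 0.6466² = 178.8.
- The interim look (rho family, rho = 3.5, at 50% information) inflates this by 1.006, to 179.9, or 180 per arm. Power at 180 per arm is 80.0% (80.3% ignoring the look).

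The stated 360 therefore reproduces, and no site term is needed to reach it.

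**Effect of site.** The document gives no site-specific rates or site sizes. I assume three equal sites (60 per arm each), mean rate 30%, true odds ratio 1 and no interim look. I also take the test to be whether the upper 95% limit lies below 1.909; the article does not spell out that rule. With p_s the event rate at site s:

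- Model SE, arm only: √[2/(180 × 0.21)] = 0.2300, whatever the spread.
- True SD of that estimator under site-stratified randomization: 0.2300 × √f, where f = 1 − mean[(p_s − 0.30)²]/0.21. To this approximation, it is also the SE of a site-standardized marginal odds ratio.
- SE of the site-conditional log odds ratio: 1/√[Σ 60 p_s(1 − p_s)/2].

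For 20/30/40%: f = 1 − 0.00667/0.21 = 0.968; true SD = 0.2263; conditional SE = 1/√(30 × 0.61) = 0.2338.

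Power at 20/30/40%:

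- arm only: Φ[(0.6466 − 1.96 × 0.2300)/0.2263] = 80.6%
- standardized: Φ[0.6466/0.2263 − 1.96] = 81.5%
- conditional: Φ[0.6466/0.2338 − 1.96] = 79.0%

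| Assumed site rates (%) | True SD | Excess of 0.2300 over it | Conditional SE | Power: arm only | Power: standardized | Power: conditional |
|---|---|---|---|---|---|---|
| 30/30/30 | 0.2300 | 0% | 0.2300 | 80.3% | 80.3% | 80.3% |
| 25/30/35 | 0.2291 | 0.4% | 0.2309 | 80.4% | 80.6% | 79.9% |
| 20/30/40 | 0.2263 | 1.6% | 0.2338 | 80.6% | 81.5% | 79.0% |
| 10/30/50 | 0.2149 | 7.0% | 0.2462 | 81.9% | 85.3% | 74.7% |

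The last row is an extreme, shown only for direction.

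**Simulation.** At 20/30/40%, simulated power was about 80.3% with arm only and 81.1% standardized. A separate simulation of the conditional analysis gave 77.6%, against 79.6% for arm only in the same runs. With the true marginal odds ratio set at 1.909, type I error with arm only fell from 0.0248 (equal sites) to 0.0176 (10/30/50%), while the standardized estimator stayed at about 0.025.

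**Scale.** At 20/30/40%, a marginal odds ratio of 1.909 corresponds to a site-conditional one of about 1.95; at 10/30/50%, to about 2.13.

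**The case against.** The strongest case against is that the article is condensed. A covariate list is ordinarily left to the statistical analysis plan, which may already name site, so a reader who infers that site is excluded goes further than the text allows. This stands. The unadjusted reading does have some textual support, because the sizing test and the interim rule are both plain two-arm odds ratios, but it is not established.

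An unadjusted analysis would also be coherent: its odds ratio is on the same scale as the sizing, the margin and the interim rule, and any error is in the safe direction for a non-inferiority claim. That stands too. Nothing the plan promises is lost.

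Two stronger readings should be resisted:

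- **That putting site in the model narrows the interval.** For the conditional odds ratio the opposite holds, because the odds ratio is non-collapsible. The gain appears only after standardizing back to the marginal scale.
- **That adjusting for age and diagnosis would raise power to 82–84%.** That needs these variables to explain 5–10% of the outcome variance, which the document does not support. Diagnosis would also need a grouping: the article lists 20 example rows, against about 108 expected events (360 × 0.30).

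**Conclusion.** The point holds as a modest improvement and not as an error. If the primary logistic regression is run without site, its standard error is about 0–2% too large for assumed spreads up to 20/30/40%, and up to about one percentage point of power is forgone. With equal site rates there is no loss. The unadjusted analysis is conservative against the marginal margin.

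The sizes rest on assumed site rates and equal site sizes. The more durable part is the scale: the plan should make clear that the odds ratio compared with 1.909 is marginal, because the obvious adjustment would change the quantity and widen the interval.

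**What to change.** Unless the statistical analysis plan already does so, specify before database close:

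1. Fit the logistic model with arm and site (three levels).
2. Standardize its predictions over the analysed patients to a marginal odds ratio, with a delta-method or bootstrap confidence interval.
3. Compare the upper limit with 1.909.
4. Use the same estimator at the interim.

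Age may be added as a further pre-specified covariate; no quantified gain is claimed for it.

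The cost is a few lines of plan wording and minor programming. Site is already recorded as the randomization stratum, so no new data are needed and the sample size is unaffected. Priority: optional to moderate.

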**Exclusion criteria**	
Nursing home patient	
Have an order for hemodialysis or peritoneal dialysis and/or listed on the patient’s problem list.	
Positive for COVID-19	
Have a discharge order	
Require intensive care unit (ICU) level of care	
A history of drug abuse	

These are examples of exclusions criteria; the final decision will be made by the local clinical teams (not the research team) to identify patients who can benefit from either ACH or traditional inpatient hospital care (i.e., clinical equipoise) based on the criteria and the judgment used in routine practice. If a patient is judged by local clinical teams not suitable for ACH or traditional inpatient hospital care, the patient cannot be randomized

If a patient is eligible, an ACH case manager or nurse will give a brief introduction of the ACH model to the patient. If the patient is interested, the case manager/nurse will complete the social stability screening (Additional file 4: Social Stability Screening) with them to make a final determination as to whether or not the patient is eligible for ACH. If the patient passes the social stability screening and is still interested in exploring the ACH option, the local clinical team will connect with a study coordinator who will inform patients in more detail of the opportunity to participate in the study, including the study purpose, procedures, risks, and benefits. Potential participants will be informed that participation in the research study is voluntary and that they are free to decline to be in the study or to withdraw from it at any point without any negative consequence. Additionally, they will be informed that the option to receive ACH or traditional brick-and-mortar hospital care will still be available to them outside of participation in the study. The study coordinators will consent and enroll patients using the attached consent form (Additional file 5).

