### Intervention

The Mayo Clinic ACH model was previously described (Paulson et al., in press) and the procedures used in the trial will be the same as those established in current routine practice. In short, the ACH program consists of three key components, linked by Medically Home’s Cesia Continuum^TM^ software platform: (1) Command Center, staffed with physicians, registered nurses (RNs), and advanced practice providers (APPs, i.e., physician assistants and advanced nurse practitioners); (2) technology in the home with custom technology kits, including biometric devices for monitoring vital signs, a custom-configured tablet with video visit capability, a telephone to facilitate 2-way communication, a backup power supply, a backup cellular communication device, and an emergency response system bracelet to keep patients and their families connected to the care team; and (3) care delivery services that include a full suite of escalation of care services, such as nurse practitioners, community paramedics, skilled nursing services, infusion therapy, phlebotomists, basic radiography technicians, and oxygen, dispatched to patients in their homes to allow for the provision of urgent and routine patient care needs.

Once a patient is randomized to the ACH arm, an admission huddle will be coordinated by the ACH physician, ACH RN, and service coordinator to plan patient-specific care and address care coordination needs. The patient will be physically transported home by community paramedics who set up the necessary technology and orient the patient and caregivers to that technology.

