Of note, minor modifications to the care process or procedures are common in routine practice and could happen during the trial in both the ACH arm and the inpatient hospital care arm, due to quality improvement efforts or other operational needs. The project aims to compare two care models already in practice, and the research team does not interfere with or control clinical teams’ day-to-day operation. Local clinical and operational teams are responsible for communicating such modifications with patients and providers, but such changes in routine practice do not need to be reported to IRB. The principal investigators will work with the project manager and study coordinators to report to IRB regarding protocol deviation and other unexpected protocol amendments beyond routine practice changes and communicate with other relevant parties.

Due to the nature of the intervention (i.e., the delivery of acute care at home versus in the brick-and-mortar hospital), criteria for discontinuing or modifying allocated intervention are not needed. If patients in the ACH arm are transferred back to the hospital during the acute phase, such events will be recorded and reported as adverse events, and if patients are re-admitted during the restorative phase, such events will be counted in the outcome, i.e., 30-day readmission. A highly pragmatic trial would allow full flexibility in how the end-users engage with the intervention in order to estimate real-world effectiveness. Therefore, this trial will not utilize additional strategies to improve adherence above what are used in routine practice to engage patients. According to previous experience in practice, the cross-over between the two care delivery models has been rare. Any cross-over events will be recorded.

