### Outcomes and follow-up

Follow-up will start from the day of randomization. It will contain two phases: the acute care phase (for the traditional inpatient care, this will last until the discharge from the hospital) and 30 days after the acute care phase. The primary outcome is a composite of all-cause mortality and 30-day readmission. The 30-day readmission will be assessed during the 30 days after the end of the acute phase. Transfers of ACH patients back to the hospital during the acute care phase will be recorded.

Secondary outcomes include individual outcomes in the composite endpoint, fall with injury, medication error, emergency room visit, transfer to ICU, cost, the number of days alive out of the hospital, and quality of life. Fall with injury will be defined based on National Database for Nursing Quality Indicators criteria (Table 5). Medication error is defined in Table 6. Quality of life will be measured by the EQ-5D during the follow-up phone call (Fig. 1).

**Table 5 Tab5:** Definition of fall with injury

Minor	Resulted in application of ice or dressing, cleaning of a wound, limb elevation, topical medication, pain, bruise, or abrasion
**Moderate**	Resulted in suturing, application of steri-strips or skin glue, splinting, or muscle/joint strain
**Major**	Resulted in surgery, casting, traction, required consultation for neurological (e.g., basilar skull fracture, small subdural hematoma) or internal injury (e.g., rib fracture, small liver laceration), or patients with any type of fracture regardless of treatment, or patients who have coagulopathy who receive blood products as a result of a fall
**Death**	The patient died as a result of injuries sustained from the fall (not from physiologic events causing the fall)

Fall with injury will be defined based on National Database for Nursing Quality Indicators (NDNQI) criteria. The primary analysis will consider all fall with injury and sensitivity analyses will be conducted to assess the severity of injury. All the clinical outcomes (e.g., fall and medication errors) are measured in routine practice. The research team will contact the clinical team if there is uncertainty about outcome adjudication

**Table 6 Tab6:** Definition of medication error

Category F	An error occurred that may have contributed to or resulted in temporary harm to the patient and required initial or prolonged hospitalization

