The fourth domain is “organization”—“What expertise and resources are needed to deliver the intervention?” The ACH trial will make use of no more than the existing staff and resources in routine practice and, thus, is very pragmatic with a score of 5.

The fifth domain is “flexibility in terms of the delivery of the intervention.” The ACH trial will leave the details of how to deliver the intervention to frontline clinicians and staff, rather than being rigidly prescriptive in the protocol. Therefore, the trial is very pragmatic, with a score of 5.

The sixth dimension is “flexibility in terms of adherence.” ACH will allow full flexibility in how the end-users engage with the intervention. Therefore, it is very pragmatic with a score of 5.

The seventh dimension is follow-up. In the ACH trial, baseline characteristics will be captured from the EHR, and outcome data will be collected via a combination of EHR and a study coordinator call enabling patient reporting. We will conduct a one-time interview at the end of the study. This hybrid approach using both EHR and patient reporting is to improve the completeness of the data, e.g., mortality, readmission, and other events outside the study sites, as well as to collect patient-reported outcomes. Therefore, we consider the trial very pragmatic with a score of 5.

The eighth dimension is “primary outcome”—measures “How relevant is the outcome to participants?” The primary outcome is the composite of all-cause mortality and readmission. The outcome is clearly important for patients, clinicians, and our health system, but since it is a composite outcome, we will give a score of 4 as “rather pragmatic” for this domain.

The ninth dimension is primary analysis. The ACH trial will use the intention-to-treat analysis with all the available data as the primary analysis and, thus, is very pragmatic with a score of 5.

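### The primary analysis is labelled intention-to-treat but admits only randomized patients who start the intervention, a post-randomization condition that can bias the non-inferiority comparison in either direction

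*Protocol article*

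**What the plan says.** The Statistical analysis section sets the population for the primary logistic regression: "Analysis will be performed on all eligible patients who provide consent, are randomized, and start the intervention, following the intention-to-treat (ITT) principle".

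Four other places in the protocol article bear on it.

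- **Discussion, ninth PRECIS-2 domain:** "The ACH trial will use the intention-to-treat analysis with all the available data as the primary analysis". No start condition appears, and the domain is scored 5 on this basis.
- **Outcomes and follow-up:** "Follow-up will start from the day of randomization".
- **Statistical analysis, per-protocol set:** "the ACH group would consider all patients who are randomized to ACH, with the follow-up censored at the time of crossing over to the control". Patients allocated to hospital care are handled in the same way.
- **Randomization:** "Due to the nature of the intervention, blinding is not feasible for trial participants and care providers".

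The Intervention section describes what follows allocation to ACH. There is an admission huddle, and then "The patient will be physically transported home by community paramedics who set up the necessary technology". The article does not say at which of these steps a patient counts as having started, nor what starting means in the hospital arm.

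**The concern.** Intention-to-treat protects a comparison because group membership is fixed by randomization and nothing later can change it. A condition on starting care lets later events decide who is counted. Patients and care providers know the allocation, so those events can depend on the arm.

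The arms are not symmetrical here. A patient allocated to hospital care is already in the emergency department or on a ward. A patient allocated to ACH still faces a huddle, transport and equipment set-up. ACH therefore plausibly has more opportunity for non-start, whether through deterioration, logistics or a change of mind.

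At stake is the one-sided 2.5% error rate for the non-inferiority claim, which randomization no longer guarantees for the set analysed. A secondary matter is power: the Sample size section gives 360 as the number required and states no allowance for excluded non-starters.

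**Working it through.** **1. The passages side by side**

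| Place | Who is included, or from when |
|---|---|
| Statistical analysis, primary | Randomized and started |
| Discussion, ninth PRECIS-2 domain | Intention-to-treat, all available data |
| Statistical analysis, per-protocol | All randomized to the arm, censored at cross-over |
| Outcomes and follow-up | Follow-up from the day of randomization |

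The first row conflicts with the second. It also leaves out patients whose follow-up, by the fourth row, has already begun. The per-protocol set takes in everyone randomized, so at entry it is wider than the set called intention-to-treat, the reverse of the usual order.

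**2. Reproducing the plan's sample size**

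Inputs from the Sample size section: 30% events in both arms, non-inferiority odds ratio (OR) 1.909, one-sided alpha 0.025, 80% power, 180 per arm.

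- Margin as a rate: 1.909 × 0.30 / (0.70 + 1.909 × 0.30) = 0.450, a risk ratio of 1.50. This agrees with the protocol.
- Wald formula on the log odds ratio: n per arm = (1.960 + 0.842)² × [2 / (0.30 × 0.70)] / (ln 1.909)², with ln 1.909 = 0.6466. This gives 178.8 per arm, or 358 in total.
- Power at 180 per arm: 80.3% (Wald), 80.1% (score test), and 80.0% with one efficacy look at half the information under rho = 3.5 spending.

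The stated 360 is reproduced.

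**3. Error rate when ACH non-starters are excluded**

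Assumptions: among all randomized patients the truth lies at the margin (control 30%, ACH 45%). A fraction f of ACH patients do not start, and their event risk is q. The documents give neither f nor q, so both are varied.

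- Analysed ACH rate: p = (0.45 − f·q) / (1 − f)
- Analysed odds ratio: OR = [p / (1 − p)] / (0.30 / 0.70)
- SE² = 1 / [180(1 − f)·p(1 − p)] + 1 / (180 × 0.30 × 0.70)
- Probability of claiming non-inferiority = Φ[(0.6466 − ln OR) / SE − 1.960]

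Worked case, f = 5% and q = 70%: p = (0.45 − 0.035) / 0.95 = 0.437, OR = 1.810, ln OR = 0.593, SE = 0.224. Then (0.6466 − 0.5933) / 0.2241 = 0.238, and Φ(0.238 − 1.960) = 4.2%.

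| ACH non-starters | q = 30% | q = 45% | q = 70% |
|---|---|---|---|
| 2% | 2.2% | 2.5% | 3.1% |
| 5% | 1.8% | 2.5% | 4.2% |
| 10% | 1.2% | 2.5% | 7.2% |

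The error rises above 2.5% only where the excluded ACH patients carry more risk than the ACH average. At equal risk it is unchanged, and at lower risk it falls.

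**4. Power when non-starters are excluded**

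Fixed-design Wald calculation, 30% in both arms, power = Φ(0.6466 / SE − 1.960), with SE² = 1 / (n_ACH × 0.21) + 1 / (n_control × 0.21).

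| Excluded | ACH only | Both arms |
|---|---|---|
| None | 80.3% | 80.3% |
| 5% | 79.2% (171 vs 180) | 78.2% (171 vs 171) |
| 10% | 78.1% (162 vs 180) | 76.0% (162 vs 162) |

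**The case against.** The strongest reply is that the practical effect is unproven and probably small. The Intervention section reports that, in earlier practice, "the cross-over between the two care delivery models has been rare". If non-start is similarly uncommon, the error rate hardly moves: with 2% of ACH patients excluded it lies between 2.2% and 3.1% over the risks shown. Starting is also undefined. If the huddle right after allocation counts, the gap in the ACH arm nearly closes. This stands as a limit on size. It does not settle the matter, because the article gives no figure for non-start, and the earlier experience comes from routine practice rather than from randomized allocation.

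Three stronger readings are tempting, and the documents do not support them.

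- **That the exclusion favours non-inferiority.** This needs excluded ACH patients to be at higher risk than the ACH average. Someone who simply changes their mind and receives hospital care at about 30% risk moves the result the other way. Deterioration before transport is not itself a primary event either. Readmission is counted only in the 30 days after the acute phase, and acute-phase transfers back to hospital are recorded as adverse events.
- **That hospital-arm patients who prefer home care would also be dropped.** Patients are told that "the option to receive ACH or traditional brick-and-mortar hospital care will still be available to them outside of participation in the study". But a patient already receiving hospital care has started, so a later move to ACH is cross-over, which the plan handles separately. Leaving the study is withdrawal, a different question.
- **That the word eligible is a second post-randomization filter.** The Study population section has the local clinical team settle eligibility before consent and randomization, and nothing in the article provides for a later review.

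It can also be said that the Discussion is only a summary and defines no analysis set. That is fair, but the conflict with the per-protocol definition lies within the Statistical analysis section itself.

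**Conclusion.** The population sentence is wrong as written: it names one principle and specifies another. It describes a modified intention-to-treat set chosen after an open allocation, and it is at odds with three other statements in the article.

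The consequence is a loss of protection, not a demonstrated bias in a known direction. Over the assumed 5% to 10% of ACH non-starters with 30% to 70% event risk, the one-sided error at the margin runs from 1.2% to 7.2% against a nominal 2.5%. These figures use a normal approximation and rest entirely on assumed fractions and risks. The power cost is modest: about 1 to 2 percentage points if only ACH loses patients, and about 2 to 4 if both arms do.

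The point should be fixed, because it defines the population that decides the trial's main claim. The likely small effect keeps it short of a critical flaw.

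**What to change.** In the Statistical analysis section, delete the condition on starting the intervention. Define the primary set as all randomized patients, analysed in the arm assigned, whether or not that care began. Take non-starters' outcomes from the electronic health record and the end-of-study call, as for everyone else.

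Report the number of non-starters and the reasons, by arm. If the started set is kept, call it modified intention-to-treat, define what starting means in each arm, and use it only as a sensitivity analysis. The Discussion's description then agrees with the analysis section.

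The cost is one sentence in the protocol, carried into the statistical analysis plan before the database closes. No new data source is needed. With all 360 analysed, power stays at about 80% and the error rate at the margin returns to 2.5%.
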